#### Secondary outcomes: all at 3 months

2.8.2

1)Levels of serum lipid profile: Significant reduction in the mean TC and triglycerides and significant increase in mean HDL-C in the intervention diet group compared to the control diet group.2)Improvements in the levels of serum inflammation markers vascular cell adhesion molecule, Intracellular Adhesion Molecule, Interleukin-6, apolipoprotein A and B in the intervention diet group compared to the control diet group.3)Safety: Frequency of AE and SAE by intervention group.4)Feasibility, adherence, and acceptability:a)the proportion of patients who complete the intervention at 3 months and time from symptom onset to intervention as a measure of feasibility;b)median MEDAS score at the end of the follow-up and adequacy of the interventions as assessed by the quantitative evaluation of the food questionnaires at 30, 60, and 90 days (percentage of adequacy) to measure adherence;c)acceptability will be assessed at 90 days using a structured questionnaire.

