### Safety

2.13

Adverse events associated with the intervention diet are collected from the time of consent until the final 3-month follow-up visit for each participant, whether considered related to the intervention study or not. All adverse events are followed up until they are resolved and are adjudicated by an independent investigator. Investigators assess any adverse effects of the interventions by administering a checklist of symptoms, including mouth symptoms, bloating, fullness, indigestion, altered bowel habits, other diet-related symptoms, and any other symptoms. Serious adverse events are defined according to International Good Clinical Practice recommendations.^[32]^ Safety specifically include all cardiovascular events (acute myocardial infarction, any stroke, cardiovascular procedures, and cardiovascular deaths) and deaths. All patients are adjudicated by an independent investigator and handled by the treating physician.

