### Statistical analyses

2.17

All efficacy analyses will be performed according to the intention-to-treat principle. The primary outcome will be compared between the 2 groups by an analysis of covariance adjusting for baseline measures unbalanced by randomization and with baseline LDL-C and statin use (initial and final doses) as covariables. To account for missing data, multiple imputations using chained equations will be used, assuming randomness. The results will be compared to those with complete data. A sensitivity analysis will be carried out to investigate the robustness of the findings according to adherence to the intervention. Safety analysis will be performed for all patients participating in the study. The number of patients with AEs, the occurrence of specific SAEs, and discontinuation due to SAEs will be tabulated. Binary outcomes, such as AEs, major cardiovascular events (acute myocardial infarction, stroke, or vascular death), or death will be analyzed with the Chi-2 test for independence. Analysis of adherence will be performed in all patients who finalized the study. The proportion of patients who completed the intervention at 3 months will be analyzed using the Chi-2 test for independence. The percentage of adequacy of the diet intervention at 1, 2, and 3 months will be analyzed with generalized linear mixed models for repeated measures. Feasibility assessed as the mean time from symptom onset to intervention will be analyzed using Student's *t* test. Analysis of the acceptability 14-item questionnaire will be performed in all patients completing the follow-up with the Mann–Whitney–Wilcoxon non-parametric test. Exploratory subgroup analyses will be carried out irrespective of whether there is a significant treatment effect on the primary outcome. These analyses will be adjusted for confounders. The following pre-specified subgroup analyses will be performed by adding an interaction term to the models: age (< or ≥ mean) years, sex, education level < or ≥12 years, post-stroke disability (modified Rankin score < or ≥1), physical activity (Rapid Assessment of Physical Activity questionnaire score < or ≥6), MEDAS score (< or ≥ median), dyslipidemia (yes/no), diabetes/insulin resistance (yes/no), BMI (< or ≥25), and BMI (< or ≥30). Per protocol analysis will be performed for the primary and key secondary efficacy outcomes, using the same statistical test as per the intention-to-treat analysis.

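### The planned safety tables count discontinuations only when due to an SAE, so no table shows how many patients stopped the diet because of a non-serious adverse event

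*Protocol article*

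**What the plan says.** Section 2.8.2 defines the safety outcome broadly: "Safety: Frequency of AE and SAE by intervention group". Section 2.13 collects AEs whether or not they are judged related to the diet, and does so by "administering a checklist of symptoms, including mouth symptoms, bloating, fullness, indigestion, altered bowel habits, other diet-related symptoms, and any other symptoms". On seriousness it states: "Serious adverse events are defined according to International Good Clinical Practice recommendations". Table 1 schedules the AE and SAE questionnaire at 30, 60 and 90 days.

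Section 2.17 then says what will be done with these data. The tables are: "The number of patients with AEs, the occurrence of specific SAEs, and discontinuation due to SAEs will be tabulated". The tests cover "Binary outcomes, such as AEs, major cardiovascular events" and death, by Chi-2. The population is set by: "Safety analysis will be performed for all patients participating in the study".

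Two other places bear on patients who stop. Sections 2.8.2 and 2.17 compare the proportion completing the intervention at 3 months, as a feasibility outcome. Section 2.4 (Consent) rules out any use of data from patients who withdraw.

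**The concern.** The collection and the tabulation point in different directions. Section 2.13 names the effects the investigators expect a diet might cause: mouth symptoms, bloating, fullness, indigestion and altered bowel habits. A patient who gives up the diet because of one of these would ordinarily not have had an SAE. Section 2.17 nevertheless restricts the one table that links stopping to harm to SAEs. This is a stated restriction and not mere silence, so it cannot be put down to the brevity of an article.

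Safety is a secondary objective (section 1.1.2), the abstract's hypothesis includes that the diet is safe and feasible, and the Discussion says the trial will help design a phase 3 trial. For that purpose, the number of patients in each arm who could not tolerate the diet is among the most useful safety figures the trial can give. As written, it is not among the planned results.

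**Working it through.** The document gives no AE rate, discontinuation rate or safety power, so there is no figure to reproduce. The check is a tracing of the text, followed by an illustration on assumed rates.

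**Step 1. Follow a patient who stops the diet because of non-serious bloating.**

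| Planned result | Does this patient appear? | With the reason for stopping? |
|---|---|---|
| Patients with AEs, with Chi-2 test (2.17) | Yes | No |
| Specific SAEs (2.17) | No | – |
| Discontinuation due to SAEs (2.17) | No | – |
| Completion at 3 months (2.8.2, 2.17) | Yes, as a non-completer | No |
| Adherence (2.17: those who finished the study) | Only if the patient stays in the study | No |
| Acceptability (2.17: those completing follow-up) | Only if the patient stays in the study | No |

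The event is counted in one place and the stop in another. No planned table joins them.

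**Step 2. Add section 2.4.** If the same patient also withdraws from the study, section 2.4 bars use of the data, while section 2.17 runs safety on all participating patients. On the first rule the patient could drop out of the any-AE count too. The two statements need reconciling. Section 2.11 encourages non-adherent patients to remain in the study, which limits how often this arises but does not settle it.

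**Step 3. Size of the gap in the discontinuation table (assumed rates).** Suppose 5 of 100 patients in an arm stop for digestive intolerance and none for an SAE.
- Planned table: 0/100 = 0%.
- Table of discontinuation due to any AE: 5/100 = 5%.
- Completion falls by 5 percentage points, with no cause attached.

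**Step 4. What pooling does to a single symptom (assumed rates).** Let p be the risk of one symptom and b the risk of any other AE, taken as equal in both arms and independent of the symptom. Then

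any-AE risk = 1 − (1 − b)(1 − p), so the between-arm difference shrinks to (1 − b)(p₂ − p₁).

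For example, with b = 0.40 and p = 0.05 vs 0.15: 1 − 0.60 × 0.95 = 0.43 and 1 − 0.60 × 0.85 = 0.49. A difference of 0.10 becomes 0.06.

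Normal-approximation power for two proportions uses n = 100 per arm (section 2.16) and alpha 0.05 (section 2.17; two-sided assumed):

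power = Φ{(|d| − 1.96·√[2p̄(1 − p̄)/n]) / √[p₁(1 − p₁)/n + p₂(1 − p₂)/n]}, where d is the difference and p̄ the mean of the two risks.

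| Symptom risk | Power, symptom alone | Any AE, b = 0.20 | Any AE, b = 0.40 | Any AE, b = 0.60 |
|---|---|---|---|---|
| 0.05 vs 0.15 | 0.656 | 0.241 | 0.133 | 0.085 |
| 0.05 vs 0.20 | 0.900 | 0.456 | 0.246 | 0.142 |
| 0.10 vs 0.25 | 0.802 | 0.432 | 0.245 | 0.145 |

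Over this assumed range, power falls from about 66–90% to about 9–46%. The trial is not powered for safety. The table shows only how far an any-AE count can hide a difference in one symptom.

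**The case against.** A reader might infer that checklist symptoms and intolerance never reach the safety result at all. The document does not support that. Section 2.8.2 counts AEs as well as SAEs, section 2.17 tabulates and tests patients with AEs without limiting them to serious ones, and the checklist in section 2.13 feeds that count. Stops for any reason also lower the completion proportion, which is compared by arm.

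Nor does the text say that non-serious AEs will be reported only as one pooled yes/no item. A breakdown by symptom is not excluded, the itemised checklist would allow it, and a symptom-level table is the kind of detail an article may leave to the full protocol or analysis plan. Its absence alone would be a weak point, and Step 4 applies only if the any-AE count is all that is reported.

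A reader might also conclude that the trial would wrongly claim almost no discontinuations due to adverse events. It would not, if the table carries the label given in section 2.17, which says SAEs. And to say that every checklist item is non-serious goes too far: the list ends with an open category, and the document gives no seriousness rates. That the named symptoms are ordinarily non-serious is a clinical judgement, though hardly a contested one.

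All of these limits stand. They do not remove the central point: the discontinuation table is expressly restricted to SAEs, and no other planned result states how many patients stopped because of a non-serious AE. Completion cannot supply it, since it mixes intolerance with every other reason for stopping.

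**Conclusion.** The concern holds in a limited form. Section 2.17 leaves stops due to non-serious AEs out of the only discontinuation-for-harm count, and names a breakdown by type only for SAEs, in a trial whose own checklist is aimed at ordinarily non-serious symptoms. The conflict between sections 2.4 and 2.17 adds to it, because patients who withdraw for intolerance might be lost from the safety counts altogether.

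The consequence is confined to descriptive safety reporting. The primary outcome, the alpha level and the sample size are untouched. The firm part rests on the wording of section 2.17 and on the judgement that the named symptoms seldom meet an SAE definition. The 0% against 5% example and the power figures rest wholly on assumed rates and should not be cited as properties of this trial.

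**What to change.** Replace the tabulation sentence in section 2.17 with wording such as: *The number of patients with any AE, with each checklist symptom, with each specific SAE, and with discontinuation of the allocated diet due to any AE (serious and non-serious shown separately) will be tabulated by arm.* The added rows should be descriptive, without further tests.

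Reconcile section 2.4 with the safety population in section 2.17, and state how AE data and the reason for stopping are handled for patients who withdraw, so that those who leave for intolerance stay in these counts as far as their consent allows.

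The cost is one sentence, one clarification and a few more rows to read. The symptom data are already gathered by checklist. The planned SAE table already requires a stop to be attributed to an event, so the change extends that attribution to non-serious events. Because the trial has been randomizing since August 2018, the team should check whether the reason for stopping was recorded for earlier patients and report any for whom it is unknown.

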To maintain diet fidelity with the intervention, in all contacts the study nutritionist emphasizes that the portions and frequencies of food of the diet assigned to the patient are respected, solve specific doubts, and inquire about AE and SAE. The food surveys are analyzed qualitatively and quantitatively by the study nutritionist in charge of carrying them out. The qualitative analysis considers the number of meals per day, fluid intake, and quality of the food consumed, which is compared to each of the diet interventions. The quantitative analysis is carried out by obtaining the ingredients and quantities of each food preparation that the patient consumes, this is then transformed into portions to obtain the intake of calories, carbohydrates, fats, and proteins. This is compared with the requirements of the assigned diet and the % of adequacy is calculated ([intake value/requirement value] × 100). An adequate intake is considered if the macronutrient is in a percentage of adequacy of 90% to 110%. We use as a reference the contributions of nutrients and calories from the “Exchange portions and Chemical Composition of foods of the Chilean food pyramid” National Institute of Food Technologies, 1999 and its update “Food Composition Table” National Institute of Food Technologies, 2018.^[31]^ This information is used to personalize each interview and adjust counselling.

As part of the institutional protocol and Chilean stroke national guidelines, all patients receive appropriate secondary stroke prevention and are discharged with an antithrombotic statin at high doses (usually atorvastatin 80 mg day, a hypotensive, and if necessary, a hypoglycemic drug). The patients are counseled at each study visit to keep their secondary prevention medications according to their treating physician prescriptions.

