### Data collection, retention, and follow-up

2.11

Data collection and follow-up assessments are performed by trained study personnel according to the schedule in the table. Patients are encouraged to stay in the study even if they are non-adherent to the assigned intervention diet and complete follow-up assessment. Extra telephone calls are performed by the study nutritionist according to the patient's needs.

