### Feasibility, adherence, and acceptability

2.12

To maintain adherence to and assess the feasibility of the intervention, participants are contacted by telephone at 1 and 2 months after recruitment. The telephone calls are made by study nutritionists to each participant to reinforce the allocated diet and administer a 24-hour diet recall questionnaire. Patients have extra telephone calls and email contacts depending on the individual evaluation of each nutritionist.

To increase adherence, randomized patients are transferred monthly an amount of money equivalent to buying avocado (2 kg per week, including family consumption) or whole grain bread (2 kg per week, including family consumption), according to the allocated diet.

The acceptability of the trial in both groups is assessed with a structured 14-item self-applied (or caregiver) questionnaire performed at the end of follow-up. Items are measured using a 5-point Likert scale.

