The results of An Avocado-Based Mediterranean Diet on Serum Lipids for Secondary Prevention after Ischemic Stroke Trial will address a gap in knowledge on the effect of dietary interventions on secondary stroke prevention.^[34]^ This pilot trial will help design a phase 3 clinical trial that could have an important impact on current stroke research and, ultimately, clinical practice, influencing dietary recommendations with important beneficial effects on cardiovascular outcomes.

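### The finishers-only adherence analysis discards 30- and 60-day recalls that the planned mixed model could use, and makes the between-arm comparison conditional on completion

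*Protocol article*

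**What the plan says.** **Analysis set.** Protocol article, section 2.17 (Statistical analyses): "Analysis of adherence will be performed in all patients who finalized the study". The same section names other sets for other purposes: intention-to-treat for efficacy and all participating patients for safety. The finishers-only set is thus a stated choice.

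**Outcome.** Section 2.8.2 measures adherence by median MEDAS at the end of follow-up and by the "quantitative evaluation of the food questionnaires at 30, 60, and 90 days (percentage of adequacy) to measure adherence".

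**Data collection.** Table 1 schedules a 24-hour recall at 30, 60 and 90 days. Section 2.12 describes the first two: "The telephone calls are made by study nutritionists to each participant to reinforce the allocated diet and administer a 24-hour diet recall questionnaire". MEDAS is taken only at baseline and at 90 days.

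**Model.** Section 2.17: "The percentage of adequacy of the diet intervention at 1, 2, and 3 months will be analyzed with generalized linear mixed models for repeated measures".

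**Related rules.** Section 2.11: "Patients are encouraged to stay in the study even if they are non-adherent to the assigned intervention diet". Section 2.4 (Consent) says that data of patients who withdraw are not used. Completion at 3 months is a separate feasibility outcome (section 2.8.2), tested between arms by chi-squared (section 2.17).

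**Purpose.** Secondary objective 4 (section 1.1.2) compares feasibility, adherence and acceptability between the diets. The Discussion adds: "This pilot trial will help design a phase 3 clinical trial".

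**The concern.** A patient who leaves after day 30 has already given one or two recalls. A repeated-measures mixed model can take such a record as it stands, but the finishers-only rule removes it first. The plan thus chooses a model that handles incomplete series and then excludes the incomplete series.

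Finishing is also a post-randomisation event that may depend on how well the patient tolerates the assigned diet. A comparison of adequacy among finishers no longer compares the groups as randomised, and it could be distorted if loss differs between arms in number or kind. No adherence analysis of all randomised patients is stated, and multiple imputation is described with the primary outcome.

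What is at stake is one secondary outcome and its use in planning phase 3, where the useful figure is adherence among all patients put on the diet.

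**Working it through.** The plan states no adherence figure, so there is none to reproduce. Only the sample size and the planned loss are taken from it.

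**Inputs from the protocol article**
- Randomised: 200, 100 per group (section 2.16)
- Planned loss: 10% (section 2.16)
- Recalls before the final visit: 2 per patient, at days 30 and 60 (Table 1, section 2.12)

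**Step 1. Recalls discarded**

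Drop-outs = 0.10 × 200 = 20. Scheduled 30- and 60-day recalls = 2 × 200 = 400. Discarded = drop-outs × recalls already given.

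| All drop-outs leave | Recalls discarded | Share of 400 |
|---|---|---|
| before day 30 | 20 × 0 = 0 | 0% |
| between days 30 and 60 | 20 × 1 = 20 | 5% |
| after day 60 | 20 × 2 = 40 | 10% |

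No 30- or 60-day MEDAS is lost, because none is collected. The discard concerns percentage of adequacy only.

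**Step 2. Possible overstatement (illustrative)**

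The protocol gives no adherence rates and no patient-level yes/no definition of adherence. Both are assumed here to show the scale. Let L be the loss, F the adherence in finishers and D the adherence in drop-outs.

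All randomised = (1 − L) × F + L × D, so overstatement = F − all randomised = L × (F − D).

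With L = 0.10 and F = 80%:

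| D (assumed) | All randomised | Overstatement |
|---|---|---|
| 80% | 0.90 × 80 + 0.10 × 80 = 80% | 0 points |
| 40% | 0.90 × 80 + 0.10 × 40 = 76% | 4 points |
| 0% | 0.90 × 80 + 0.10 × 0 = 72% | 8 points |

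If drop-outs adhered better than finishers, the sign would reverse: D = 90% gives 0.10 × (80 − 90) = −1 point.

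**Step 3. Unequal loss (illustrative)**

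Assume 15% loss in one arm and 5% in the other, with F = 80% in both. Finishers then show no difference between arms.
- D = 40%: 0.85 × 80 + 0.15 × 40 = 74% against 0.95 × 80 + 0.05 × 40 = 78%, a gap of 4 points.
- D = 0%: 0.85 × 80 = 68% against 0.95 × 80 = 76%, a gap of 8 points.

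The 15% and 5% are assumptions; the protocol gives only 10% overall.

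**The case against.** The case for leaving the plan alone has several parts.

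- **Finishing the study is not the same as keeping to the diet.** Non-adherent patients are encouraged to complete follow-up, so non-adherent finishers stay in the analysis. This stands and limits any bias. It does not make loss unrelated to adherence.
- **Unequal drop-out would be visible.** A reader might infer from step 3 that the plan hides an 8-point difference between arms. The documents do not support that. The 15% and 5% are invented, 8 points is the extreme with drop-outs at 0%, and the separate completion test would show 85% against 95%. That test does not, however, recover the discarded recalls or make the adequacy comparison one of the groups as randomised.
- **The direction is not established.** It is tempting to say that the rule overstates adherence. That is the expected direction if drop-outs adhere less, but the protocol has no data on it. Percentage of adequacy is also two-sided: section 2.7 counts intake above 110% of requirement as inadequate too, so an upward bias in a mean adequacy is not well defined.
- **Few data are involved.** At 10% loss it is at most 40 of 400 recalls, and possibly none. This stands.

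A reader might also infer that leavers should simply be counted as not adherent. That does not fit either planned measure, median MEDAS or percentage of adequacy. The 90% to 110% band applies per macronutrient and is described as serving to tailor counselling. The rule would also class deaths and unrelated withdrawals as dietary failure, and partly repeat the completion outcome.

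**Conclusion.** The point holds in a limited form. Section 2.17 excludes usable 30- and 60-day recalls from an analysis whose model could take them, and nothing else in the article repairs this. At the planned 10% loss the discard is 0 to 40 of 400 recalls. The between-arm adequacy comparison becomes conditional on completion.

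An overstatement of adherence is plausible but not shown. On the assumed yes/no measure with 80% adherent among finishers, it is 0 to 8 points at 10% loss, depending on how drop-outs behave.

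Nor should the trial be read as one whose main purpose is feasibility. Its primary aim is LDL-C in a superiority design, and adherence belongs to the fourth secondary objective. The primary conclusion is not touched. The change is still worth making: it is cheap, and the outcome is pre-specified and bears on the planning of phase 3.

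**What to change.** 1. In section 2.17, replace the finishers-only rule for adequacy with wording such as: *Percentage of adequacy will be analysed by allocated arm in all randomised patients with at least one recall, using every available 30-, 60- and 90-day record in the mixed model. An analysis limited to patients who finished the study will be supportive.*
2. Reconcile section 2.4 with this. As it stands, recalls of withdrawn patients would remain excluded whatever section 2.17 says, which also sits badly with the intention-to-treat statement. At the least, keep data collected before a patient is lost or stops, where consent allows.
3. Report adequacy beside the completion proportion, and state that the denominator of the latter is all randomised patients. Among finishers it would be 100% by construction.
4. Do not add a rule that counts leavers as not adherent, since no patient-level yes/no adherence outcome is defined.

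This does not remove every problem. Patients with no recall stay outside the model, and the model still relies on later missing values being predictable from what was observed.

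The cost is a short edit to two sections and one added supportive analysis. No new data are needed. Reported adherence may become slightly less favourable.

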**Conclusion::**

We hypothesize that an Avocado-based Mediterranean diet will further reduce the levels of LDL-cholesterol at 3 months compared to the control diet, and that the intervention is safe and feasible.

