MeDi improves lipid profile, insulin sensitivity, glycemic control and decreases blood pressure, and new-onset diabetes, all strong risk factors for stroke.^[17,18]^ Furthermore, there are several beneficial nutrients abundant in the MeDi that could act on inflammatory biomarkers such as adhesion molecules, cytokines, or molecules related to the stability of atherosclerotic plaque.^[19]^ On the other hand, Avocados, although not part of the classical MeDi, are another nutrient-dense source of MUFA, rich in vitamins, minerals, fiber, phytosterols, and polyphenols. A meta-analysis of randomized clinical trials showed that Avocado-substituted diets significantly decrease the levels of total cholesterol (TC), low-density lipoprotein cholesterol (LDL-C), and triglycerides.^[20]^ A comprehensive review on the effect of Avocados concluded that they can be used as dietary supplements for the treatment of different components of the metabolic syndrome.^[21]^ No evidence exists on the effect of Avocados on stroke prevention.

Lowering LDL-C levels prevent ischemic stroke recurrence in an inverse linear relationship, without a floor effect.^[22]^ Interventions to further decrease LDL-C levels show significantly lower recurrence rates of stroke.^[23–26]^

Our primary aim is to demonstrate a reduction in LDL-C in patients who had a recent (1 month) ischemic stroke receiving a MeDi based on Avocados compared to a low-fat high-complex carbohydrate diet after 3 months. Secondary aims include the safety and feasibility of the interventions.

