### Trial design

2.1

Prospective, randomized, open-label, blinded outcome assessment (PROBE design), investigator-driven, controlled superiority clinical trial.

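### The diet is hypothesised to be safe and feasible, but the only inference named for either claim is a between-arm difference test, which can establish neither

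*Protocol article*

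**What the plan says.** The Abstract's conclusion states the hypothesis in absolute terms: "the intervention is safe and feasible". The Introduction places this below the lipid question: "Secondary aims include the safety and feasibility of the interventions". Section 2.1 describes an "investigator-driven, controlled superiority clinical trial", and Section 2.16 sizes it for LDL-C alone.

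Section 2.8.2 defines the two outcomes. The safety outcome is "Safety: Frequency of AE and SAE by intervention group". The feasibility outcome is "the proportion of patients who complete the intervention at 3 months and time from symptom onset to intervention as a measure of feasibility". Neither comes with an acceptable excess of harm or a target.

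Section 2.17 names the analyses. Adverse events, major cardiovascular events and death are compared between arms by chi-square. For completion: "The proportion of patients who completed the intervention at 3 months will be analyzed using the Chi-2 test for independence". "Feasibility assessed as the mean time from symptom onset to intervention" is compared by Student's t test. Patients with adverse events and specific serious events are also counted in tables. For stopping, the article says only that "discontinuation due to SAEs will be tabulated".

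**The concern.** A difference test asks whether two arms can be told apart. The hypothesis asks something else: whether the rate of harm is acceptably low and whether enough patients can follow the diet. A non-significant result answers neither question, and for uncommon events in a trial of this size it is the likely result even if the true rate doubles.

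The Discussion describes the study as a pilot that will help design a phase 3 trial. That use needs the completion proportion and its precision, not a p-value between arms.

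The discontinuation table has a separate gap. The checklist in Section 2.13 asks about mouth symptoms, bloating, fullness, indigestion and bowel habits. These are the symptoms most likely to make someone give up a diet, and they are rarely serious adverse events. A table limited to serious events would leave out stopping for intolerance.

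**Working it through.** **Inputs.** 100 patients per arm (Section 2.16); alpha 0.05 (Section 2.17), taken as two-sided. The article gives no expected event or completion rates, so every rate below is an assumption shown over a range.

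**The plan's own figure.** The only sample size stated is 100 per arm for LDL-C. With SD 9.4 and difference 4.6, n = 2(1.96 + 0.84)² × 9.4² / 4.6² ≈ 66 per arm. Inflating for loss and crossover in several ways gives 74 to 91, so 100 is not reproduced exactly. That is a separate matter. No power or precision is stated for safety or feasibility.

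**Completion.** If 60 of 100 complete in each arm, the observed difference is 0, chi-square is 0 and p = 1. The same holds for any equal pair, so the test carries no information on the level of completion. The interval does:
- one arm at 90%: 1.96 × √(0.9 × 0.1 / 100) = 5.9 points either side
- one arm at 60%: 1.96 × √(0.6 × 0.4 / 100) = 9.6 points either side
- difference with both arms at 90%: 1.96 × √(2 × 0.9 × 0.1 / 100) = 8.3 points either side

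**Power of the chi-square test.** With p̄ the mean of the two rates, power = Φ{[|p1 − p2|√n − 1.96√(2p̄(1 − p̄))] / √(p1(1 − p1) + p2(1 − p2))}. For 2% v 4%: (0.200 − 1.96 × 0.2412) / 0.2408 = −1.13, so power is 0.13. The exact column enumerates all outcomes of the uncorrected test.

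| Assumed rates, 100 per arm | Approximate | Exact |
|---|---|---|
| Events 2% v 4% | 13% | 11% |
| Events 5% v 10% | 27% | 27% |
| Events 10% v 20% | 51% | 52% |
| Adverse events 30% v 50% | 83% | 83% |
| Completion 90% v 80% | 51% | 52% |
| Completion 90% v 75% | 80% | 82% |

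At 90 per arm these fall by up to about 5 points. With 5% events in one arm, 80% power needs about 17% in the other. Detecting 5% v 10% with 80% power needs 435 per arm.

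**What an interval adds.** Suppose 5 and 10 events occur per 100. The chi-square p-value is 0.18. The risk difference is 5 points, with standard error √(0.05 × 0.95 / 100 + 0.10 × 0.90 / 100) = 0.0371 and 95% CI −2.3 to 12.3 points. The p-value alone hides that an excess of 12 points has not been excluded. Even 0 events in 100 leaves a one-sided 95% upper limit of 1 − 0.05^(1/100) = 3.0%.

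**Time to intervention.** The stroke must precede randomisation by no more than a month (Section 2.3), the nutritionist is told the diet after consent, and the diet starts at home (Section 2.7). The interval from onset to allocation is balanced in expectation by randomisation; only the part from allocation to diet start can be affected by arm. The overall distribution is therefore the more informative summary of feasibility.

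**The case against.** The strongest reply is that the article nowhere says a non-significant test will count as proof. A reader might infer that rule from the hypothesis and the list of tests, but no sentence links them, and it should not be attributed to the authors.

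Nor do the tests stand alone. Events are tabulated by arm and adjudicated by an independent investigator, and adherence and acceptability have their own measures. The feasibility outcome is itself a proportion, so poor completion in both arms would be visible. The secondary objectives in Section 1.1.2 are worded as comparisons with the control diet, so a comparison is not out of place. All of this stands. It means the data will be there to read, but it does not supply an inference that fits the claim.

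Other strong readings also go too far:
- Power is not low throughout. It is low for uncommon harms and modest completion gaps, and adequate for large differences.
- Intolerance will not go unrecorded. Symptoms are collected at 30, 60 and 90 days, and patients with adverse events are tabulated. What is missing is the link from non-serious events to stopping.
- One might say that time to intervention is mostly fixed before allocation. That is plausible, but the article does not give the split.
- One might take the 10% loss in Section 2.16 as a completion target. It inflates the LDL-C sample size. Section 2.29's equivalent on retention in the article, Section 2.11, keeps non-adherent patients in follow-up, so loss and non-completion of the diet differ.

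Success thresholds may sit in the full protocol or the SAP, so their absence here is not held against the article.

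**Conclusion.** The point holds in a limited form. The article makes an absolute claim and names, as its only inference on these outcomes, tests that cannot support it. For completion the mismatch is logical and needs no assumed rate: two equally poor arms give p = 1. For safety it is a matter of size: about 13% to 27% power for a doubling from 2% or 5%, and about 83% for 30% v 50%, all on assumed rates, 100 per arm and a two-sided 5% test. The discontinuation table is narrower than the symptom checklist that it should draw on. The primary LDL-C analysis is not affected. This is a low-cost improvement to stated methods and does not threaten the trial's main result.

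**What to change.** Change the wording of Section 2.17, or settle it in the SAP:
- Report risk differences with 95% confidence intervals for adverse events, serious adverse events, major cardiovascular events and death. Word the safety conclusion by the excess that the interval excludes.
- Give completion in each arm with its 95% confidence interval as the feasibility result. Do not use the 10% sample-size allowance as a success threshold.
- Describe time from onset to intervention in all randomised patients by median and interquartile range, with any comparison between arms secondary.
- Tabulate discontinuations due to any adverse event, with serious events as a subset.
- State that p > 0.05 is not evidence of safety or feasibility.

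The existing tests may stay. No extra patients or visits are needed; the one item to confirm is that the reason for stopping is recorded for non-serious events. The cost is that the safety and feasibility statements will be more cautious.
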